#### 2.6.4 Attention Control Group (AC)

This group performs a home-based program of the same stretches utilized in the ACTIVAS group. The stretching protocol consists of one set of 3-4 static stretching exercises held for 30 seconds and performed three days per week. As flexibility exercises are low-intensity, low-impact and low-volume, minimal caloric expenditure is expected to be incurred. To increase compliance and aid in the standardization of the home-based stretching, participants are provided a booklet of the flexibility exercises (35, 36). Participants are shown how to use the booklet and instructed in the stretching exercises by an exercise trainer prior to the intervention. In addition, participants are asked to complete weekly records of flexibility compliance and physical activity performed outside the study. The AC group is followed throughout the 12-month study duration and are completing activity logs during this period. At 12 months, the AC group are invited to participate in Phase 1 of the ACTIVAS intervention. If elected, participants attend one additional testing visit after the 16-week exercise intervention at week 65. The assigned trainer follows up with each participant on a weekly basis by phone call, email, or text message to assess program adherence, answer any questions, and document barriers to continue in the study.

#### 2.6.5 Intervention Adherence

If exercise sessions are missed, make-up sessions are scheduled as soon as possible with no more than four supervised sessions allowed per week. All participants are given an additional two weeks beyond the 16-week supervised intervention period to make up for any exercise sessions missed due to illness, work, travel etc. Participant adherence to the ACTIVAS program will be captured by, 1) percentage and number of prescribed sessions attended (participants must attend ≥80% of sessions to be considered compliant with ACTIVAS program e.g., ≥38 sessions), and 2) average minutes of exercise/week (participant must complete ≥80% of prescribed minutes) performed at the prescribed intensity.

#### 2.6.6 Adverse Events

Any expected and unexpected adverse events are reported to the principal investigator who then subsequently reports to the institutional review board. Serious events must be reported within 24 hours of occurrence or finding out about the event. All adverse events, both serious and non-serious, and deaths that are encountered from initiation of study intervention, throughout the study, and within 30 days of the last study intervention are followed to their resolution, or until the participating investigator assesses them as stable or determines the event to be irreversible, or the participant is lost to follow-up. The presence and resolution of adverse events are documented on the appropriate case report form and recorded in the participant’s medical record. Furthermore, given the remote nature of the exercise sessions, additional safety precautions include: 1) providing safety recommendations specific to exercises and/or assessments (i.e., standing near a wall for balance activities), 2) adapting the exercise protocol as necessary (i.e. limit weight, changing resistance exercise modality), 3) verifying address of remote exercise location (i.e., home address), should study staff need to call 911 in an emergency, and 4) ensuring that emergency contact information of the participant is up-to-date and readily available.

### 2.7 Outcome Measures

Testing is completed across two days at time points baseline (Week 0), post-phase 1 (Week 17), post-phase 2 (Week 33), and post-phase 3 (Week 49), with only one day required for testing at all mid-point assessments (Week 9, 25, 41). A complete data collection schedule is provided in **Figure 4**. All measures are collected at all time points and both groups unless specified below. Participants will be provided with monetary compensation (25$) for each testing timepoint attended, and parking validation for every visit to DFCI. All measures that have a verified Spanish version will be used for those who are Spanish speaking and/or would prefer to complete testing in Spanish.

**Figure 4 f4:**
[figure not shown]
SPIRIT flow diagram for study visits timeline of the ROSA Trial. DEXA, dual-energy x-ray absorptiometry; AC, attention control group. *Only for the AC who choose to complete the ACTIVAS program.

#### 2.7.1 Primary Outcomes

Metabolic dysregulation is assessed as (a) insulin resistance (primary endpoint), (b) visceral adiposity, and (c) frequency of metabolic syndrome.

Homeostasis Model Assessment (HOMA) is used to estimate insulin resistance using fasting plasma levels of glucose and insulin (37). Due to cost and the invasive nature of directly quantifying insulin resistance (e.g. glucose clamp), we chose to use HOMA as a surrogate measure of insulin resistance, which is a validated measure in clinical studies (38).

A whole-body dual-energy x-ray absorptiometry (DEXA) (*Hologic Inc., Marlborough, MA*) scan is used to assess visceral adiposity, in addition to measures of whole body and appendicular and whole-body fat and lean mass (kg). Although central obesity is generally defined as a waist circumference >80 cm in women (39), capturing an image of visceral adiposity tissue provides a more accurate portrayal of central obesity. DEXA is strongly correlated with computed tomography (40) and is a practical and quick method of assessing visceral adiposity among breast cancer survivors. Automated visceral adiposity analysis is used to quantify the volume (cm^3^) of visceral adiposity tissue in the abdomen. DEXA is only to be performed at testing visits during baseline, post-phase 1, post-phase 2 and post-phase 3, and will not be performed during mid-phase assessments (**Figure 4**).

Frequency of metabolic syndrome is captured based on the metabolic syndrome criteria accepted by the American Heart Association (AHA), consisting of hypertension, high waist circumference, and elevated levels of serum HDL-cholesterol, triglycerides, and fasting glucose (39):

- Blood pressure (BP) is measured using an automated device with an appropriately sized cuff (*Omron BP 786, Lake Forest, IL*) after the participant has sat quietly for five minutes while resting their arm on a table so the brachial artery is level with the heart.- Waist circumference (cm) defined as the distance around the waist using the umbilicus as the reference point and is assessed with a constant-tension tape measure.- Lipid profile and fasting glucose are obtained from a fasting (12 hour fast) blood draw by a DFCI nurse or phlebotomist. After being treated and aliquoted, the blood serum and plasma samples are stored in a -80°C freezer for future batch-tested analysis. Analysis of bloods through commercially available ELISA kits (*ThermoFisher Scientific, Waltham, MA*) will be used. A multitude of cancer-related biomarkers will be examined including but not limited to leptin, IL-6, TNF-a, adiponectin, estradiol, and SHBG.

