### 2.9 Sample Size Calculation

We propose to randomize 160 subjects (n=80/group). We assume 15% attrition (which is exceptionally conservative given our retention rates of >90%) (80) at the primary endpoint (4-months). With this sample size, we consider the study is sufficiently powered to detect a between-group difference. Specifically, the primary efficacy variable of this study is change in HOMA-IR from baseline to 4-month). From the preliminary results (80), we anticipate the standard deviation of HOMA-IR change from baseline is 6.9. The study will have 80% power, at a two-sided 0.05 alpha level, to detect a 3.3 difference in HOMA-IR change from baseline between the groups.

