### 2.10 Statistical Analysis

The primary analysis population is all randomized subjects based on the intention-to-treat principle. The secondary analysis population is the per-protocol set. To test hypotheses related to differences in MetD outcomes across groups at the primary endpoint (4-month), we will use two-sample t-test for the continuous outcomes (HOMA-IR and VA) and Fisher’s exact test for the binary outcomes (diagnosis of metabolic syndrome). For HOMA-IR and VA, we will calculate change from baseline at 4-month for each subject and estimate mean difference between groups and corresponding 95% confidence interval. For diagnosis of metabolic syndrome, we will estimate the proportion of participants with metabolic syndrome at 4-month for each group and compare it between groups. Odds ratios and corresponding 95% confidence interval will be used to summarize the magnitude of the effect of the intervention. ANCOVA and logistic regression models will be also used to compare each of these outcomes at 4-month between groups, conditioning on potential prognostic factors, such as menopausal status, age, BMI, months since end of treatment, history of diabetes, type of treatment (chemotherapy vs radiation vs both), surgery type (lumpectomy, mastectomy), previous history of physical activity prior to diagnosis, and family medical history self-reported.

These primary endpoints are measured longitudinally. We will fit the longitudinal data with generalized mixed-effects models. The identical link and logistic link will be used for continuous and binary outcomes, respectively. The group indicator, time, and other covariates will be included in the models as the fixed effects. Some of the covariates (e.g., menopausal status) will be time-dependent covariates. Measures of physical fitness, functional capacity, and patient-reported QOL outcomes will be also analyzed in the same way.

Subgroup analyses will be conducted to assess the heterogeneity of the intervention effect on each outcome. The following factors will be considered: menopausal status, age, BMI, months since end of treatment, previous diabetes.

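### The metabolic syndrome definition lists elevated HDL-cholesterol as a component, contradicting the AHA criteria it names; coded literally, it would reverse the diagnosis of some women

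*Protocol article*

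**What the plan says.** Section 2.7.1 (Primary Outcomes) sets out three parts: "Metabolic dysregulation is assessed as (a) insulin resistance (primary endpoint), (b) visceral adiposity, and (c) frequency of metabolic syndrome". For part (c), the defining sentence opens with a named standard, "Frequency of metabolic syndrome is captured based on the metabolic syndrome criteria accepted by the American Heart Association (AHA", and cites a reference for it. The same sentence then lists five components, "consisting of hypertension, high waist circumference, and elevated levels of serum HDL-cholesterol, triglycerides, and fasting glucose".

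The bullets that follow describe measurement only. For the blood components the article says "Lipid profile and fasting glucose are obtained from a fasting (12 hour fast) blood draw". It gives no HDL cut-off or direction, and no number of components needed for a diagnosis.

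Section 2.10 (Statistical Analysis) uses the resulting diagnosis. It plans Fisher's "exact test for the binary outcomes (diagnosis of metabolic syndrome") and states that "we will estimate the proportion of participants with metabolic syndrome at 4-month for each group and compare it between groups". Odds ratios, logistic regression, a longitudinal mixed model and subgroup analyses use the same outcome.

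**The concern.** In the list, the word elevated governs HDL-cholesterol as well as triglycerides and glucose. For triglycerides and glucose a high value is adverse. For HDL a low value is adverse. This is general knowledge of the syndrome and needs no figure from the cited source. One of five components therefore points the wrong way, in text that defines an analysed outcome and is not mere background.

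If a programmer followed the list, a woman with low HDL would lose a criterion she should meet, and a woman with favourable HDL would gain one. A rise in HDL across the cut-off would count towards metabolic syndrome. If exercise raises HDL, this would push the exercise group towards more diagnoses and could hide or offset a real benefit on this outcome.

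**Working it through.** **1. The article's own figure, and whether it is touched.** The article states no power or expected rate for metabolic syndrome. Its only power statement is for change in HOMA-IR (Section 2.9): "We propose to randomize 160 subjects (n=80/group"), "We assume 15% attrition", SD 6.9, difference 3.3, two-sided alpha 0.05, power 80%.

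- Evaluable per group: 80 × 0.85 = 68.
- Standard error: 6.9 × √(2/68) = 1.183.
- Power (normal approximation): Φ(3.3/1.183 − 1.96) = Φ(0.829) = 0.796. The exact t-test gives 0.791.

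The stated 80% is reproduced to within a percentage point. HOMA-IR uses glucose and insulin, not HDL, so nothing here changes it.

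**2. Whose diagnosis would change under literal coding.** Assume a diagnosis at 3 or more of 5 components, and one HDL cut-off, so that elevated is the exact complement of low. The article states neither. Let k be the number of the other four components present.

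- k ≤ 1: at most 2 in total, so no diagnosis either way.
- k ≥ 3: diagnosis either way.
- k = 2: HDL alone decides, so reversing it reverses the diagnosis.

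There are C(4,2) = 6 ways to have k = 2, each with two HDL states, so 12 of the 32 component patterns change and the other 20 do not.

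**3. How many women that could be.** The article gives no component prevalences, so these are assumed: waist criterion met with probability w = 0.9 to 1.0; blood pressure, triglycerides and glucose each met with probability q = 0.3 to 0.6; all independent.

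P(k = 2) = w × 3q(1−q)² + (1−w) × 3q²(1−q)

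| q | w = 0.9 | w = 1.0 |
|---|---|---|
| 0.3 | 0.416 | 0.441 |
| 0.4 | 0.418 | 0.432 |
| 0.5 | 0.375 | 0.375 |
| 0.6 | 0.302 | 0.288 |

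The range is about 29–44%. Unequal prevalences can also fall near the top: with waist 100%, blood pressure 50%, triglycerides 35% and glucose 35%, the share is 0.5×0.65×0.65 + 2×(0.5×0.35×0.65) = 0.439.

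**4. Effect on the group comparison.** Assume that low HDL is present in 50% of controls and 35% of the exercise group, that it is independent of the other components, and that exercise changes nothing else. With correct coding the difference (exercise minus control) is P(k=2) × (0.35 − 0.50). With reversed coding it is P(k=2) × (0.65 − 0.50).

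- P(k=2) = 0.288: −4.3 points correct, +4.3 points reversed.
- P(k=2) = 0.441: −6.6 points correct, +6.6 points reversed.

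In this illustration HDL is the only thing that moves, so the sign of the effect changes. If exercise also improved other components, those gains would still be counted correctly and the net result could go either way.

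**The case against.** The strongest reply is that the sentence is governed by the AHA criteria and the list is a careless paraphrase of them. The list cannot be coded as it stands, because the article gives no cut-offs and no component count. Anyone deriving the outcome must go to the cited criteria or the full protocol, where the direction would be right. This stands as to consequence: a drafting slip is the most likely explanation, and nothing shows that the data will be scored the wrong way. It does not remove the contradiction inside the defining sentence. The absence of cut-offs and a component count is not itself a fault, since an article commonly leaves these to the full document.

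A reader might infer more than the article supports:

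- *That the trial will score HDL improvement as worsening.* This would require the named standard to be ignored. Even then only a rise across the cut-off matters, and only where HDL is decisive.
- *That 44% of women would be misclassified.* That figure is the top of a range built on assumed prevalences and independence. Eligibility in Section 2.2 has a BMI limit but no waist limit, and the 100% in Section 3 refers to either metabolic syndrome or central obesity in an earlier sample of 40. A waist prevalence of 100% is therefore an assumption. With a separate, higher cut-off for elevated HDL, women with intermediate values would be classified the same way under both readings, and fewer would change.
- *That the main result is at risk.* The designated primary endpoint does not use HDL.

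**Conclusion.** The point holds as an error of definition. Section 2.7.1 names a standard and then states one of its five components in the wrong direction, for an outcome that Section 2.10 tests between groups, and nothing elsewhere corrects it.

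The bias is conditional on literal coding. Under the assumptions in the working, it would reverse the diagnosis of about 29–44% of women and could move the estimated effect against exercise. Confidence is high for the wording error; the article gives no basis for judging how likely literal coding is. Sample size, power and the HOMA-IR analysis are untouched.

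**What to change.** In Section 2.7.1, change the component list to read *reduced HDL-cholesterol, and elevated triglycerides and fasting glucose*, in line with the cited criteria. Before analysis, confirm that the derivation of the outcome, wherever it is programmed, scores HDL below the cut-off as meeting the criterion.

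The cost is one line of text and one check of the derivation. Samples are stored for later batch testing, so the check can be made before the outcome is derived. No visit, sample, test or sample size changes.

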#### 2.7.2 Secondary Outcomes

##### 2.7.2.1 Anthropometrics

Height (cm) is assessed using a stadiometer with shoes removed. Hip circumference (cm), defined as the distance around the widest girth of the buttocks using the greater trochanter as a landmark, is measured with a constant tension tape measure. Weight (kg) and body composition is assessed using bioelectrical impedance (*Tanita 780, Arlington Heights, IL*), with shoes and socks removed, providing both appendicular and whole-body measures of fat and lean mass (kg). Height and weight are used to calculate body mass index (BMI, kg/m^2^).

##### 2.7.2.2 Cardiopulmonary Fitness and Exercise Capacity

To assess VO_2peak_ a maximal CPET is completed on a cycle ergometer (*ErgoSelect 100, Ergoline, Germany*) using an incremental ramp protocol (41, 42). Participants complete a 5-minute warm-up at a resistance of 40W then proceed into an incremental ramp protocol increasing 10W every minute until volitional fatigue. Cadence is maintained between 60 and 80 revolutions per minute (41, 42). Heart rate (*Polar USA, Lake Success, NY*) and rate of perceived exertion (RPE; Borg scale 1-10) are recorded every minute and at cessation of test. Expired gas analysis (*TrueOne 2400, ParvoMedic Inc., Salt Lake City, UT*) is used to measure VO_2peak_. The results of this test are also used to calculate the target heart rate to achieve the prescribed exercise intensity during the aerobic program.

The 6-minute walk test is used to estimate exercise capacity (43, 44). Participants are instructed to walk as far as they can in 6-minutes walking up and back a 10m walking course within a hallway. Distance achieved in six minutes is measured in meters.

##### 2.7.2.3 Muscular Strength

Isometric handgrip strength is measured in the dominant upper limb (*Camry Digital Hand Dynamometer, El Monte, CA*). Participants perform three trials in a standing position with their arms down by their side with the highest result used for analysis.

Muscular strength is assessed by estimated 1RM calculated from 10RM of leg press and chest press (*Matrix Fitness, Cottage Grove, WI*). Additionally, 10RM is completed for each of the six resistance intervention exercises prescribed so that an accurate intensity may be prescribed: 1) chair squat, 2) floor chest press, 3) glute bridge, 4) seated bent over row, 5) lunges, and 6) shoulder press. Participants perform 1-2 warm-up sets of 6-8 repetitions. The participant proceeds to complete sets of 10 repetitions with increasing weight each set until volitional fatigue is reached on the 10^th^ repetition. The weight of the participant’s 10RM is recorded in kilograms and used to estimate 1RM using validated equations (45, 46).

##### 2.7.2.4 Physical Function

Physical function is assessed using the short physical performance battery (SPPB) (47), timed up and go (TUG) (48), gait speed (49), Margaria stair climb (50), and sit-to-stand (51) tests. The SPPB is comprised of three sections: 1) balance with feet together, semi tandem, and full tandem is held for up to 10 seconds (s) with no support. Only one attempt is given for each position, and the time (s) to complete is recorded; 2) usual gait speed over 4m is timed where the participant completes two attempts with the fastest time (s) recorded; and 3) chair stand where the time (s) to complete five chair sit-to-stands is recorded, only one attempt is given, after a familiarization practice. Each section of the SBBP is given a score dictated by performance to then provide a summary score. The TUG test times how fast it takes a participant to stand up from a chair, walk around a cone placed 3m away from a chair where they start, and end in a seated position. Participants attempt the TUG three times, after a familiarization practice, where the average of the three trials is calculated. Gait speed is assessed over a 6m flat surface where the time to walk the 6m course at a usual and fast pace is recorded. Two attempts for each speed are completed. The Margaria stair climb is completed in a stairwell of ten stairs. The participant walks/runs up the stairs as fast, and safely, as they can. The time (s) the participant takes from stair three to stair nine is recorded; three attempts are given after a familiarization practice, where the average time of the three trials is calculated. Power (kg) is calculated from the stair climb using a validated equation (50). The sit-to-stand test involves participants completing as many sit-to-stands from a seated chair position to a standing position with full hip extension in 30 s; one attempt is given, with number of full movements with correct technique recorded.

##### 2.7.2.5 Lymphedema

Lymphedema has been defined in recent literature as a greater than 10% difference in volume calculation for the arm compared to the uninvolved upper extremity (52). Lymphedema is assessed using geometric arm volume calculations on both upper limbs (52). Circumferential measurements are taken with a constant-tension tape measure at the following anatomic landmarks: axillary fold, halfway between axillary fold and antecubital fossa, antecubital fossa, halfway between antecubital fossa and wrist, and wrist. Calculations for limb geometric volume are performed using the frustum (truncated cone) volume as described by Taylor et al. (52). A percentage difference between lymphedema limb and the uninvolved limb is calculated to determine the amount of lymphedema.

##### 2.7.2.6 Shoulder Function and Range of Motion

Upper body function is assessed using the Y Balance Test Kit (*Move2Perform, Evansville, IN*) (53). Participants begin in a three-point plank position on toes or knees depending on ability. The tested shoulder is the supporting limb placed on the connecting block, the non-testing limb is placed on the medial block, and feet are placed shoulder-width apart. From this position, the participant uses their non-testing limb to move each reach block one at a time in the medial, inferolateral, and superolateral directions in a controlled manner as far as they can and then return to the starting position. The test is performed three times on each side with 30s rest between trials. The reach distance of each direction is recorded where the highest value of each direction is used to calculate an average composite score.

Bilateral upper body strength and power is assessed through the seated medicine ball throw (SMBT) (54). Participants are instructed to sit on the floor with their head, shoulders, and back against the wall and legs extended; legs may be bent if ability does not allow for full extension. To calculate a relative throwing distance, arm reach distance is measured from the wall in meters. Using a two kg medicine ball covered in chalk, the participant performs a chest pass holding the ball with both hands and throwing it forward in a straight line as far as they can with head, shoulders, and back maintaining full contact with the wall. A measuring tape is used to measure the distance from the wall to the most proximal point of the chalk mark with the participant’s reach distance subtracted to provide a final distance in meters. Three test trials will take place after a practice throw with a 1-minute rest between each trial. The average of the three trials will be calculated.

Shoulder function is assessed through the shoulder performance test (SPT) using the following tasks: overhead reach, hand behind the head, and hand behind the back. All movements are completed in a standing position starting with arms by side. The time(s) taken to complete the respective tasks with the correct technique 20 times is recorded. Each task is repeated right and left.

Upper body function is assessed using the closed kinetic chain upper extremity stability test (CKCUEST) (55). Participants begin in a three-point plank position on toes or knees, depending on ability, with hands 36 in. (91.4 cm) apart, shoulders perpendicular to hands, and feet hip-width apart. From this position, the dominant hand reaches across the body, touches the non-dominant hand, and returns to the starting position. Subsequently, the same movement is performed by the non-dominant hand. Participants are instructed to perform as many alternating touches as possible in 15s while maintaining the correct push-up position. Three trials occur after practice with 45s of rest in between each trial.

Shoulder active range of motion (AROM) is measured on both upper limbs. Using a goniometer (*Jamar E-Z Read*), AROM is assessed in external rotation at 0°, external rotation at 90°, forward flexion, and abduction (56, 57). The participant stands for all tests except for external rotation at 90° where the participant is lying on the ground with knees bent and feet hip-width apart. The starting position of the measured limb is dictated by AROM being tested. The participant is asked to actively perform the required motion with the angle of movement recorded in degrees. Three active trials are performed after the tester passively moves the participant’s limb in the tested motion.

Upper limb musculoskeletal disorders are assessed using the Disabilities of the Arm, Shoulder, and Hand (DASH). DASH is a 30-item questionnaire designed to measure physical function and symptoms of possible musculoskeletal disorders of the upper limb (intraclass correlation coefficient = 0.96; 95% CI = 0.93-0.98) (58).

